### Lifestyle measurements

The IMEVID instrument (Instrument for measuring lifestyle in people with diabetes) will be applied. It consists of 25 closed questions grouped into 7 dimensions: Nutrition, Physical Activity, Tobacco Consumption, Alcohol Consumption, Information on Diabetes, Emotional Management, and Compliance with Treatment. Each item presents three response options with scores of 0, 2, and 4, where 4 corresponds to the maximum desirable value in each response, for a total score from 0 to 100. (27) The IPAQ Instruments, Diabetes-39 questionnaire, and IMEVID instrument are validated instruments in Spanish.

### Clinical management

The health professionals of each clinic (physician and/or nutritionist) will have credentials to access the clinical management platform “I Understand my diabetes” to capture sociodemographic, comorbidity, clinical, biochemical, anthropometric, body composition, lifestyle, quality of life, diet, and physical exercise data. From these data, the system will provide a diet and a physical exercise plan previously designed by physicians and nutrition researchers participating in the platform, considering the clinical data recorded by the health professionals. This clinical management system of the health professional can be seen in Figure 2.

**Figure 2 F2:**
[figure not shown]
Patient clinical information.

All participants will receive a personalized dietary plan, designed by dietitians, based on their current weight and comorbidities. The plan will consist of 15%–20% protein, 50%–55% carbohydrates, and 25%–30% fat, with saturated fat accounting for less than 7% of total calories. The menus will range from 1,200–2,600 calories, tailored to address common comorbidities in individuals with diabetes, such as dyslipidemia, hypertension, and kidney disease, as well as personal preferences, dietary habits, and economic considerations.

### Randomization

Randomization of patients for the clinical trial will be performed using the National Cancer Institute's online statistical software, available at: https://ctrandomization.cancer.gov/tool/. Participants from each of the six clinics will be randomly assigned to one of the following three groups:
*Group with educational website program (*Figure 3*)**Group with mobile app* *+* *educational website program (*Figure 4*)**Group with usual care*

**Figure 3 F3:**
[figure not shown]
Educational website program.

**Figure 4 F4:**
[figure not shown]
Mobile app.

### Group with educational website program

Participants will receive the educational intervention with the website called “I Understand my diabetes”, designed by a group of clinical experts in diabetes, including physicians, nutritionists, diabetes educators, and epidemiologists. This educational site was previously validated through expert consensus and usability testing in individuals with type 2 diabetes (17, 28). The content, images, videos, and exposure time were previously validated through expert consensus, along with the usability, comprehensibility, and perceived usefulness among individuals with diabetes from the clinics where the intervention will be implemented. The educational course is available on the Moodle platform at https://entiendomidiabetes.org/.

The intervention includes ten interactive modules on topics such as diabetes education, pharmacological treatment, glycemic control indicators, nutrition, myths and facts about diabetes, complications, depression, and family support. Each module integrates visual aids, concise text, and videos to facilitate comprehension. Interactive activities within each module are designed to reinforce learning and promote active self-management of type 2 diabetes (T2D).

Participants will review one module per week, completing all modules in an organized manner over a two-month period. Thereafter, unrestricted access to the modules will remain available, allowing participants to revisit those of preference during the study follow-up period. At each in-person visit, emphasis will be placed on the modules reviewed and any questions regarding their content will be addressed. In addition, participants will receive a dietary plan tailored to their current weight and comorbidities, along with prototype menus to support dietary adherence. Upon completion of all modules, participants will be awarded a certificate of completion.

### Group with mobile app + educational website program

Participants assigned to this group will have access to the mobile app, where they can view their personalized diet and exercise plan, monitor their glucose and weight, and receive reminders to take the medications prescribed by their doctor. This group will have access to the website, and the aim is to improve adherence to drug treatment and lifestyle changes. The app displays the prescribed caloric intake and classifies foods using a color-coding system based on food group and glycemic index. In addition, participants will be able to make food exchanges that will allow them to vary their diet. They will also be able to see the evolution of their BMI and track their glucose and A1c levels as recorded by their treating physician. The app includes tools for physical activity, such as exercise routines and timers, as well as reminders for medical appointments. It records visits to the meal plan and tracks the times set aside for physical activity. The app was developed using a responsive architecture that enables real-time synchronization between healthcare professional management and the app. It incorporates interactive elements and full keyboard navigation. The follow-up system provides quantifiable metrics of therapeutic adherence through time-stamped records of medication intake, self-monitoring of blood glucose, nutritional tracking based on food exchanges, and physical activity. The app is currently undergoing usability testing, as shown in Figure 4.

### Group with usual care

Participants in the control group will receive general nutritional recommendations for following a healthy diet, as well as general measures for diabetes care. General physical activity recommendations will follow national diabetes care guidelines. In order to minimize follow-up losses, a communication link will be established with each participant's primary care provider, who will encourage continued participation. Appointments will be scheduled flexibly, and participants will receive reminders through the mobile app and follow-up calls.

### Follow-up and procedures

The study will last 12 months. Participants will attend a face-to-face consultation every 3 months, as shown in Figure 5.

**Figure 5 F5:**
[figure not shown]
Follow-up and procedures.

**Primary measurements**: A1c (Basal and 12 months).

**Secondary measurements**: Lipid profile. Anthropometry and body composition. Lifestyle. Quality of Life. Physical Activity Level. (Basal and 12 months). Medical and Nutritional Therapy. In the baseline phase, participants will receive a complete plan that will include dietary and physical exercise recommendations, together with the collection of sociodemographic, clinical and biochemical data. Blood pressure will be taken, and relevant questionnaires will be administered. At 12 months, biochemical and anthropometric data will be reevaluated, and appropriate instruments will be applied. Follow-up visits will be scheduled at 3 and 6 months to reinforce medical and nutritional interventions.

At baseline, a comprehensive assessment will be conducted, including dietary and physical activity recommendations, collection of sociodemographic, clinical and biochemical data, blood pressure measurements and administration of standardized questionnaires. These evaluations will be repeated at 6 and 12 months. Additional follow-up visits at months 3 and 6 will reinforce interventions. Visit time points and assessments are summarized in Table 1.

**Table 1 T1:** Schedule of assessments.

Measurements during the intervention		Months			
	Basal	3	6	9	12
Medical examination to obtain sociodemographic and clinical data, measurement of systolic and diastolic blood pressure	X				
Biochemical data in blood samples (A1c, glucose, serum creatinine, total cholesterol, triglycerides, LDL-c and HDL-c).	X				X
Measurements of body weight, height, waist circumference, fat percentage, fat mass and lean mass	X	X		X	X
Medical and nutritional therapy, 24 h food reminder record.	X	X		X	X
Lifestyle (IMEVID), Quality of Life (Diabetes 39) Physical Activity Level (IPAQ)	X		X		X
Creation of users to the educational website and/or mobile App	X^a^				
Telephone call to reinforce the intervention group			X		

a For groups with educational website and mobile app + educational website.

The inclusion and follow-up of participants in the study is shown in Figure 6. The study follows the Standard Protocol Elements for Randomized Clinical Trials guidelines.

**Figure 6 F6:**
[figure not shown]
Flow diagram of the study. The expected flow of patients with diabetes in the different phases of the study.

### Results of the study

Primary objective. To evaluate the effect on metabolic control through the measurement of A1c levels and fasting glucose before and after 12 months of intervention. The measurement will be considered a continuous variable to identify achievement in metabolic control from A1c (≤7%). Secondary objectives. To assess changes in lipid profile (total cholesterol, LDL-c, HDL-c, and triglycerides), and body composition (weight, BMI, fat percentage, fat mass, and waist circumference. After the intervention, it will be possible to compare the clinically significant results of the metabolic variables in control targets: HbA1c % (≤7%), fasting glucose mg/dl (≤130), cholesterol mg/dl (≤200), LDL-cholesterol mg/dl (≤100), HDL-cholesterol mg/dl (≥40 men and ≥50 women) and triglycerides mg/dl (≤150).

The assessment of lifestyle through IMEVID, validated in the population with diabetes in Mexico, will be treated as a categorical variable, ranging from adequate and regular to inadequate lifestyle. Quality of life will be assessed through Diabetes-39, which includes different components of quality of life and will be analyzed as a categorical variable.

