### Design and setting

A randomized controlled trial with three parallel groups, will be conducted across seven family medicine clinics of the Mexican Social Security Institute in Mexico City. The duration of intervention and follow-up is 12 months, with evaluations at baseline, 3, 6, 9 and 12 months. This study complies with international ethical standards and was approved by the National Research and Ethics Commission of the Mexican Social Security Institute, under the registration number R-2018-785-100. The clinical trial considers the effect of the mobile app + website vs. the website alone and a control group. It assumes a minimum clinically important difference (MCID) of 0.5% in HbA1c at 12 months. Based on the findings reported by Duke et al. (Cochrane 2009; ref. 23), who reported modest mean reductions in HbA1c with individual education (−0.3% in participants with a baseline HbA1c > 8%), a reduction of 0.5% was considered; a standard deviation (SD) of 1.3% was assumed based on reports from primary care cohorts and registry data, where the SD of HbA1c typically ranges from 1.1% to 1.3%. Using the formula to compare two means with *α* = 0.05 (two-tailed) and 80% power: *n* per group = 2 × (Z1 − *α*/2 + Z1 − *β*)2 × *σ*2/*Δ*2 With Z1 − 0.025 = 1.96, Z0.80 = 0.84, *σ* = 1.3, and *Δ* = 0.5, the required sample size was 106 participants per group. Taking into account a 20% loss, this resulted in 133 per group, and for greater conservatism, 136 participants per group were recruited (22).

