### Quality of life measurements

Quality of life will be measured using the Diabetes-39 questionnaire, which has been validated in the Mexican population. The questionnaire contains 39 items distributed in five sections: Energy-Mobility, Diabetes Control, Anxiety Concern, Social Burden, and Sexual Functioning. It is scored on a scale from 1 to 7, (1 for not at all affected and 7 for extremely affected in quality of life). The score of each section is transformed to a scale from 0 to 100 using a formula for linear conversion (26).

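### Diabetes-39 and IMEVID are scored 0–100 but are to be analysed as categories, which discards within-category change and lowers power on two secondary objectives by an amount the plan does not fix

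*Protocol article*

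**What the plan says.** The Objectives section of the protocol article lists quality of life (Diabetes-39) and lifestyle (IMEVID) among the secondary objectives.

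Both instruments yield numeric scores. For the five Diabetes-39 sections, Quality of life measurements states: "The score of each section is transformed to a scale from 0 to 100 using a formula for linear conversion". For IMEVID, Lifestyle measurements describes 25 items scored 0, 2 or 4, "for a total score from 0 to 100".

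Results of the study then sets the scale of analysis. IMEVID "will be treated as a categorical variable, ranging from adequate and regular to inadequate lifestyle". For Diabetes-39: "Quality of life will be assessed through Diabetes-39, which includes different components of quality of life and will be analyzed as a categorical variable". It names three IMEVID classes without cut-points and no Diabetes-39 categories.

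Statistical analysis assigns ANOVA or Kruskal-Wallis to clinical, anthropometric and biochemical variables, and a chi-square test to metabolic control goals. It names no test for either questionnaire. The only power calculation, in Design and setting, is for A1c.

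**The concern.** A participant whose score improves but who stays in the same class counts as unchanged, and two participants at opposite ends of a class count as equal. An analysis of the score uses these differences; an analysis of the classes cannot. The scores exist in any case, because the classes must be derived from them, so the loss buys no saving in data collection.

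The choice also sets the questionnaires apart from the other outcomes. The article treats A1c as a continuous measure as well as against a target, and compares the other clinical measures on their own scales. Only the questionnaires are given as categories alone. At stake is the trial's ability to detect a real effect on two of its listed secondary objectives.

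**Working it through.** **Inputs from Design and setting (all for A1c).** Difference: "It assumes a minimum clinically important difference (MCID) of 0.5% in HbA1c at 12 months". Spread: "a standard deviation (SD) of 1.3% was assumed based on reports from primary care cohorts and registry data". Error rates: α = "0.05 (two-tailed) and 80% power". Result: "the required sample size was 106 participants per group".

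**Reproducing the plan's figure.** n = 2 × (1.96 + 0.84)² × 1.3² / 0.5² = 2 × 7.84 × 1.69 / 0.25 = 105.997, so 106 per group. With 20% loss, 106 / 0.8 = 132.5, so 133. The planned 136 leaves 136 × 0.8 = 108.8, about 109, for analysis. The stated figures hold.

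**Assumption.** No effect or SD is given for the questionnaires. As an illustration, take the A1c standardised effect, d = 0.5 / 1.3 = 0.385, a normally distributed score, and a pairwise comparison with 106 per arm. Category proportions below are for the two arms pooled.

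**Continuous score.** Power = Φ(d√(n/2) − 1.96) = Φ(0.3846 × 7.280 − 1.96) = Φ(0.84) = 80.0%; 79.6% with the t distribution.

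**Median split.** The proportions above the cut are Φ(±0.192) = 0.576 and 0.424, a difference of 0.1525. The standard error is √(2 × 0.25 / 106) = 0.0687 under the null and √(2 × 0.576 × 0.424 / 106) = 0.0679 under the alternative. Power = Φ((0.1525 − 1.96 × 0.0687) / 0.0679) = Φ(0.26) = 60%.

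**Three equal levels.** The arms have proportions 0.403 / 0.333 / 0.264 and the reverse. The noncentrality is 106 × 4 × 0.0693² / 0.333 = 6.1, against 2.80² = 7.84 for the continuous score.
- Nominal chi-square, 2 degrees of freedom, critical value 5.99: power 59.3%.
- Ordinal test, 1 degree of freedom, with the same noncentrality: Φ(√6.1 − 1.96) = Φ(0.51), or 69.6%.

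**Other splits (106 per arm, d = 0.385; loss measured against 79.6%).**

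| Pooled split | Nominal chi-square | Loss (points) | Ordinal test | Loss (points) |
|---|---|---|---|---|
| 33/33/33 | 59.3% | 20.3 | 69.6% | 10.0 |
| 25/50/25 | 59.8% | 19.8 | 70.1% | 9.5 |
| 20/60/20 | 58.1% | 21.5 | 68.5% | 11.1 |
| 10/60/30 | 56.7% | 22.9 | 66.9% | 12.7 |
| 5/25/70 | 48.3% | 31.3 | 58.0% | 21.6 |

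With 109 per arm, each power is about 1 point higher and the losses are nearly unchanged.

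**Varying the effect and the number analysed.** For d from 0.30 to 0.50 and 106 to 136 per arm, the pairwise loss with two or three levels runs from about 3 points (d = 0.50, 136 per arm, balanced levels, ordinal test) to about 31 (d = 0.385, 106 per arm, 5/25/70, nominal test).

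**Three-arm global test (d = 0.385 between the extreme arms, 106–109 per arm).** ANOVA has 70–84% power, depending on where the middle arm lies. Chi-square on three equal levels has 48–63%, a loss of about 21 to 23 points.

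None of these figures includes baseline adjustment, whose gain depends on a baseline-to-12-month correlation that the article does not give.

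**The case against.** The strongest reply is that the loss cannot be read off this plan. The effect is borrowed from A1c, the splits are unknown, and chi-square is named only for metabolic control goals. IMEVID has three ordered levels, so an ordinal test is a natural reading and roughly halves the loss when the levels are reasonably balanced. Both outcomes are secondary and no power is claimed for them. A categorical analysis is less efficient but valid. All of this stands, and it is why the size is given as conditional.

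A reader might go further in three ways that the article does not support:

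- **That categorising prevents adjustment for the baseline score.** It does not. A logistic or ordinal model can include the baseline score, and Statistical analysis already plans an adjusted logistic model for dichotomised A1c.
- **That cut-points will be chosen after the data are seen.** An article may leave cut-points to the full protocol or analysis plan, which is not shown. Their absence here says nothing about when they will be set.
- **That the same criticism reaches the IPAQ activity levels.** The comparison made here concerns only the two instruments with 0–100 scores, so nothing is concluded about IPAQ.

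What the reply does not answer is why a score should be replaced by its classes in the analysis. The article gives no reason, and every scenario examined shows some loss.

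**Conclusion.** The point holds as a matter of efficiency. The article commits two instruments with 0–100 scores to categorical analysis, which discards information on two secondary objectives. If the true effect is about 0.385 SD and 106–109 per arm are analysed, pairwise power falls from about 80% to about 57–62% with a median split or a three-level nominal test, and to about 67–71% with an ordinal test. These ranges exclude very lopsided splits such as 5/25/70. Across the wider assumptions the loss is roughly 3 to 31 points.

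A flat statement that the plan costs 20 points would be too strong: that figure needs an effect, cut-points and a test that the article does not supply for these outcomes. The sample size calculation and the primary A1c result are untouched. The change is worth making because it costs almost nothing.

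**What to change.** In Results of the study, state that the main analysis of each instrument is the continuous 0–100 score at 12 months, for the five Diabetes-39 sections and the IMEVID total, compared between arms by ANCOVA adjusted for the baseline score. Add the questionnaires to Statistical analysis accordingly. Keep the three IMEVID classes, and any Diabetes-39 categories, as descriptive tables.

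The cost is wording only. Table 1 already schedules both instruments at baseline and 12 months, and the scores are part of the stated scoring. The small downside is that effects are reported as score differences rather than shifts between classes; the descriptive tables still show those shifts.

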### Statistical analysis

Descriptive statistics will be used with measures of central tendency and dispersion for quantitative variables that have a parametric distribution; variables with free distribution will be reported in median and interquartile range and will be presented in summary measurement tables. One-way ANOVA or Kruskal Wallis test will be used to compare the effect on clinical, anthropometric, and biochemical variables between groups. An X^2^ test will be used to evaluate the effect of the intervention between groups for metabolic control goals. An intention-to-treat analysis will be performed for the three groups in the clinical trial. In addition, a per-protocol analysis will be performed on the outcome variables according to compliance with the interventions. To this end, the level of compliance with the educational modules will be measured, as well as the use of the mobile application. A repeated measures ANOVA test will also be performed to analyze the effect of the intervention in each of the groups. A logistic regression model will be used to identify the effect of the intervention on the primary target variable, A1c, as a dichotomous variable in glycemic control and uncontrol. It will be adjusted for other variables, such as intervention group, years of diagnosis, physical exercise, schooling, marital status, and occupation.

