### Anthropometry and body composition measurements

Anthropometry will be recorded by two previously trained nutritionists and standardized according to the method proposed by Habitch and the specifications described by Lohman et al. (23, 24) Weight (kg) and height (cm) will be obtained for the calculation of BMI in an Inbody® device (model BPMO40S12F07). Additionally, WC will be measured at the midpoint between the lower rib and the upper edge of the superior iliac crest on the right side. Hip circumference (HC) will be measured at the greater diameter of the trochanters. The measurements will be recorded three times and the mean value of the second and third measurements will be used for analysis.

Body composition will be assessed using bioelectrical impedance analysis (BIA). At the UMF 20 clinic, measurements will be obtained with the InBody 120 device (InBody Co.), while at the remaining sites (UMF 1, 4, 7, 9, and 10), an Omron body composition monitor (Omron Healthcare) will be used.

All measurements will be performed under standardized conditions. Participants will be instructed to fast for at least 8 h, refrain from alcohol, caffeine, and strenuous exercise for 24 h prior to the assessment, and empty their bladder immediately before the test. Measurements will be taken with participants in light clothing, barefoot, and standing upright, following the manufacturer's operating guidelines for each device. The InBody 120 applies a multifrequency electrical current through hand and foot electrodes, while the Omron devices use a single-frequency current with footplate electrodes. Both methods estimate body composition using proprietary algorithms. The following variables will be recorded: body weight (kg), body mass index (BMI), body fat percentage (%), fat mass (kg), skeletal muscle mass (kg), and total body water (liters) will also be documented. To ensure consistency and reproducibility, all measurements will be conducted by trained personnel, using the same device for each participant at baseline and follow-up visits.

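### The planned between-arm tests for A1c carry no baseline or clinic term, which is valid but inefficient, and the adjusted logistic model does not fix when its physical-exercise covariate is measured

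*Protocol article*

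**What the plan says.** All references are to the protocol article.

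- **Between-arm test (Statistical analysis).** "One-way ANOVA or Kruskal Wallis test will be used to compare the effect on clinical, anthropometric, and biochemical variables between groups". Biochemical variables include A1c. Attainment of metabolic targets is compared by a chi-square test. A repeated-measures ANOVA is added, worded as an analysis within each group.
- **Adjusted model (Statistical analysis).** A logistic regression is planned for A1c as controlled or uncontrolled. On covariates the text says: "It will be adjusted for other variables, such as intervention group, years of diagnosis, physical exercise, schooling, marital status, and occupation".
- **Allocation (Randomization).** "Participants from each of the six clinics will be randomly assigned to one of the following three groups".
- **Availability of covariates (Follow-up and procedures, Table 1).** A1c is measured at baseline and 12 months, and the IPAQ at baseline, 6 and 12 months.
- **Role of physical activity.** The Objectives list it as a secondary outcome. The description of the app arm includes exercise routines and timers.
- **Devices (Anthropometry and body composition measurements).** "At the UMF 20 clinic, measurements will be obtained with the InBody 120 device (InBody Co"; the other listed sites use an Omron monitor. Each participant keeps the same device at baseline and follow-up.
- **Sizing (Design and setting).** "It assumes a minimum clinically important difference (MCID) of 0.5% in HbA1c at 12 months"; "a standard deviation (SD) of 1.3% was assumed based on reports from primary care cohorts and registry data"; "the required sample size was 106 participants per group".

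**The concern.** Entry A1c may lie anywhere above 7% and below 13%, so participants start far apart, and where they start should predict where they finish. A between-arm test that ignores the starting value leaves that predictable variation in the error term. Any chance imbalance at baseline also goes uncorrected. The same applies, to a lesser degree, to differences between clinics. For body composition, one clinic uses a different device and technology from the others, so final values pooled without a clinic term carry any device offset as noise.

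The logistic model raises two further questions. Its named covariates include marital status and occupation but not baseline A1c, the obvious predictor of reaching 7% or below. They also include physical exercise with no time point. A baseline value is a legitimate covariate. A follow-up value could itself be changed by the intervention, and conditioning on it would remove whatever part of the effect acts through exercise. The resulting odds ratio would then not describe the total effect of the intervention.

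**Working it through.** **1. The plan's own sample size.** The inputs come from Design and setting: difference 0.5, SD 1.3, two-sided alpha 0.05, 80% power, z values 1.96 and 0.84.

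n = 2 × (1.96 + 0.84)² × 1.3² / 0.5² = 2 × 7.84 × 1.69 / 0.25 = 105.997, that is 106 per group, as stated. With a 20% loss, 106 / 0.8 = 132.5, that is 133, raised to 136; 3 × 136 = 408. All the figures reproduce. The formula assumes no covariate adjustment, so the unadjusted analysis is consistent with the sizing.

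**2. Completers.** 136 × 0.8 = 108.8, taken as 108 per arm.

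**3. Power of one pairwise comparison under three analyses.** The article gives no baseline-to-12-month correlation r, so the range is an assumption. The SD is taken as 1.3 at both times. Power is from the two-sided t test with 108 per arm.

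- Final values: SD = 1.3. The standard error is 1.3 × √(2/108) = 0.177, and power is 80.3%.
- Baseline-adjusted (ANCOVA): residual SD = 1.3 × √(1 − r²).
- Change scores: SD = 1.3 × √(2(1 − r)).

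| Assumed r | ANCOVA SD | ANCOVA power | Change SD | Change power |
|---|---|---|---|---|
| 0.3 | 1.240 | 83.9% | 1.538 | 66.2% |
| 0.4 | 1.191 | 86.6% | 1.424 | 72.9% |
| 0.5 | 1.126 | 90.1% | 1.300 | 80.3% |
| 0.6 | 1.040 | 94.0% | 1.163 | 88.2% |
| 0.7 | 0.928 | 97.6% | 1.007 | 95.3% |

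ANCOVA has the highest power at every r. Change scores are worse than final values below r = 0.5 and equal to them at 0.5. The normal approximation gives results within half a percentage point of these (80.7% on final values, for example).

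**4. The same gain as sample size.** With exact z values the unadjusted requirement is 107 per group. With baseline adjustment it is 97, 90, 80, 68 and 55 for r = 0.3 to 0.7.

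**5. The clinic term for A1c.** The article gives no intraclass correlation (ICC), so 0.01 to 0.10 is assumed, with arms balanced within clinic. Leaving clinic out makes a nominal 0.05 test run at about 0.049 (ICC 0.01), 0.048 (0.02), 0.044 (0.05) or 0.039 (0.10), which is conservative. Power (normal approximation) with versus without the term is 81.1% v 80.8% (ICC 0.01), 82.6% v 81.3% (0.05) and 84.6% v 81.9% (0.10). The gain is under 3 points.

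**6. The exercise covariate.** No arithmetic is possible: the article gives nothing from which to size the share of the effect that runs through exercise. Set side by side, the IPAQ is scheduled at baseline, 6 and 12 months, physical activity is an outcome that the app is meant to change, and the model description does not say which measurement enters.

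**The case against.** **The unadjusted test is not wrong.** It is valid under randomisation, its type I error already allows for chance baseline imbalance, and it matches the formula that sized the trial. This stands. The gain is power above the planned level, and its amount depends on a correlation that the article does not give.

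**Baseline may already be used.** The primary objective speaks of changes in A1c, so the ANOVA may be on change, and a repeated-measures ANOVA is also planned. This stands in part. The article does not say which values enter the ANOVA, so a comparison against final values alone would be one-sided; both are shown above. The repeated-measures analysis is worded as within each group, so as written it supplies no baseline-adjusted contrast between arms.

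**The covariate list is open.** It is introduced as a set of examples, so baseline A1c and clinic are not excluded. That is fair, but they are named for no analysis, while less prognostic variables are.

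**Exercise may be a baseline value.** A reader might infer that the model conditions on exercise measured after randomisation and is therefore biased. The text does not support this as a fact: no time point is given, the IPAQ is also taken at baseline, and the neighbouring covariates are entry characteristics. What remains is an ambiguity that permits a harmful reading.

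**Clinic and device matter little.** For A1c this is right. For body composition, keeping one device per participant makes a constant offset cancel in change scores, so the device argument applies only to final values.

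**Conclusion.** The point holds as an improvement that costs nothing, together with one needed clarification. It is not an error that invalidates the analysis or the sample size.

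For a difference of 0.5, SD 1.3 and 108 completers per arm, baseline adjustment raises pairwise power from about 80% on final values to about 84–98% over assumed correlations of 0.3 to 0.7. It beats change scores throughout, by about 18 points at 0.3 (83.9 − 66.2) and about 2 points at 0.7 (97.6 − 95.3). The clinic term adds under 3 points for A1c at assumed ICCs up to 0.10. It is more useful for final body-composition values, where it would absorb an additive device offset.

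In the logistic model, the absence of baseline A1c and clinic from the named covariates and the undated exercise covariate should be put right. The documents establish neither that a follow-up exercise value will be used nor how much of the effect it would remove, so no figure for that bias is warranted.

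**What to change.** 1. Make the primary analysis a linear model of 12-month A1c on arm, baseline A1c and clinic, and report the pairwise differences between arms with 95% confidence intervals. This also settles whether final or change values are analysed.
2. Use the same form, with the outcome's own baseline value, for the other continuous outcomes. For body composition the clinic term then also covers the device difference.
3. In the logistic model for A1c of 7% or below, add baseline A1c and clinic, and state that physical exercise enters only as the baseline IPAQ value.
4. Before clinic is defined as a factor, reconcile the number of clinics: seven under Design and setting, six under Randomization.

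The cost is wording in the analysis section or the statistical analysis plan, ideally fixed before outcome data are seen. Baseline A1c, clinic and baseline IPAQ are already to be collected, and the sample size does not change.
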